### ***Power***

Our sample size is determined primarily by pragmatic considerations and logistical constraints. A total of **58 LTC homes** will be included in the trial: a maximum of 38 homes allocated to receiving the full intervention and 20 homes to receiving usual care. After grouping homes sharing providers together, we anticipate a total of 45 independent clusters (30 intervention, 15 control). For our primary outcome measured as an **ordinal** variable (number of days with antipsychotic prescription in the past 7 days), 45

homes with 2:1 allocation will yield 80% power to detect a cumulative Odds Ratio (i.e., odds of being in a higher category) of 0.6, assuming an intracluster correlation coefficient (ICC) of 0.01 and an average of 120 residents per home. Assuming that 30% of control arm patients will have 7 days of antipsychotic prescriptions, an OR of 0.6 implies a reduction in this proportion in the intervention arm to 20%.

To ensure we will be able to detect clinically important differences with adequate power for our secondary prescribing outcome (measured as a **dichotomous** variable), we used a simulation study with 1000 simulation runs to determine the required effect size (difference in change from baseline to 6 months in antipsychotic prescribing between the arms) that can be detected with at least 80% power. For this simulation, we assumed a conservative ICC of 0.1, an average of 120 residents per home, and a control arm proportion of 30%. With 45 homes (30 intervention, 15 control), we will have **83.4%** power to detect an OR of approximately 0.75 at 6 months. Assuming a control arm proportion of 30%, this OR corresponds to a reduction in the intervention arm to approximately 25%.

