### **Analysis**

Descriptive statistics will be calculated for all variables of interest: continuous variables with a normal distribution will be described using means and standard deviations (medians and inter-quartile ranges in the case of skewed distributions), whereas categorical variables will be summarized using frequencies and proportions. All analyses will be by Intention To Treat. Analyses will be conducted using SAS v.9.3 and statistical significance will be assessed at the 5% level.

The **primary outcome** describing **dispensing of medication** (number of days with antipsychotic/benzodiazepine/antihypertensive/anticholinergic prescriptions in the last week) will be analyzed using generalized linear mixed effects regression with multinomial distribution and cumulative logit link. To account for the staggered implementation of the intervention, phase (phase1/phase2) will be included as a fixed effect. Random intercepts and slopes will be specified to account for intracluster

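### The 80% power stated for the primary ordinal outcome does not follow from its inputs: at the printed ICC of 0.01 power is above 99%, and the ICC of 0.1 in the next paragraph is not reconciled with it

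*Protocol*

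**What the plan says.** The Power section of the protocol sizes the trial on practical grounds and then reports what that size can detect. After homes with shared prescribers are grouped, "we anticipate a total of 45 independent clusters (30 intervention, 15 control"). For the primary outcome (days with an antipsychotic in the past week, 0 to 7), the claim for these units is: "homes with 2:1 allocation will yield 80% power to detect a cumulative Odds Ratio (i.e., odds of being in a higher category) of 0.6". The clustering inputs follow in the same sentence: "assuming an intracluster correlation coefficient (ICC) of 0.01 and an average of 120 residents per home". The effect is put in context by a premise about the control arm, "Assuming that 30% of control arm patients will have 7 days of antipsychotic prescriptions". From this premise the section concludes that "an OR of 0.6 implies a reduction in this proportion in the intervention arm to 20" per cent. The Analysis section adds that "statistical significance will be assessed at the 5% level".

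The next paragraph of Power deals with the secondary dichotomous outcome, any antipsychotic in the past month: "For this simulation, we assumed a conservative ICC of 0.1, an average of 120 residents per home, and a control arm proportion of 30" per cent. It reports 83.4% power for an OR of about 0.75, from 1,000 simulated trials in which the arms are compared on change since baseline.

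The protocol does not give the split of the other 70% of control residents over 0 to 6 days, the method behind the 80%, or the between-period correlation used in the simulation.

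**The concern.** The primary outcome has the larger target effect (OR 0.6 against 0.75) and an ICC ten times smaller, on the same clusters and the same cluster size. Yet it is given slightly less power (80% against 83.4%). Either the 80% or one of its inputs must be off.

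This is the only power statement for the primary outcome. The number of homes is fixed by logistics, so what is at stake is how sensitive the trial is understood to be. If ICC 0.01 is right, the trial can detect effects well short of OR 0.6. If 0.1 is right, sensitivity depends on the category distribution and on how much the baseline data contribute, and the protocol states neither for this outcome.

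**Working it through.** **Inputs from Power and Analysis.** 30 and 15 clusters; 120 residents each, so 5,400 in all (3,600 and 1,800); OR 0.6; 30% of controls at 7 days; 5% level, taken as two-sided (an assumption, since sidedness is not stated).

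**Intervention proportion.** Odds 0.30/0.70 × 0.6 = 0.257, so 20.45%. This agrees with the protocol's 20%.

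**Design effect.** 1 + (120 − 1) × ICC: 2.19 at 0.01 and 12.9 at 0.1.

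**Attempt to reproduce the 80%.** Whitehead's proportional-odds formula with 2:1 allocation is

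V = (5,400/DE) × (2/27) × (1 − Σp̄³), z = |ln 0.6| × √V = 0.511 × √V, power = Φ(z − 1.96),

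where p̄ is the mean of the two arms' probabilities in each category.

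The least favourable split puts the whole 70% in one category. Merging categories can only raise Σp̄³, because (a + b)³ ≥ a³ + b³. With everyone at 0 or 7 days, p̄ = 0.748 and 0.252, and Σp̄³ = 0.434.

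- ICC 0.01: V = 2,465.8 × 0.0741 × 0.566 = 103.4; z = 5.19; power 99.9%.
- The same with p̄ weighted 2:1: Σp̄³ = 0.4585; z = 5.08; power 99.9%.
- A two-proportion test of 30% against 20.45% on 822 and 1,644 effective residents (1,800/2.19 and 3,600/2.19): 99.9%.
- A cluster-level t-test simulation: 99.9%.

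Every other split gives more. The 80% is therefore not reproduced.

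**Variants at ICC 0.01.** Using 58 × 120/45 = 155 residents per cluster still gives above 99.9%. A coefficient of variation of cluster size as large as 1.0 gives 97.9% or more. A change-from-baseline contrast with no between-period correlation, which doubles the variance, gives 95.5%. None comes near 80%.

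**What 80% power would mean at ICC 0.01.** Solving for the OR gives about 0.76 (70/30 split) to 0.81 (even spread). At OR 0.6, about 12 to 15 clusters would be enough (76.7% and 85.0%).

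**The same comparison at ICC 0.1, 6-month data only, OR 0.6.** The splits are assumptions, because the protocol gives none.

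| Control residents not on 7 days (70%) | Power |
|---|---|
| All at 0 days | 53–58% |
| 60% at 0 days, 10% on days 1–6 | 63–66% |
| 50% at 0 days, 20% on days 1–6 | 69–72% |
| 10% at each of days 0–6 | about 80% |

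The ranges cover normal and t (43 df) reference distributions and equal or 2:1 weighting of p̄. For the last row, Σp̄³ = 0.0249, V = 418.6 × 0.0741 × 0.975 = 30.2, z = 2.81, power 80.2%.

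**Credit for baseline at ICC 0.1 (0/7-day split).** The correlation of cluster means between periods is r = c × (120 × 0.1/12.9) = 0.93c, where c is an assumed cluster autocorrelation. The variance is multiplied by 1 − r² (baseline as covariate) or 2(1 − r) (change score). Power is about 55–68% at c = 0.5, 85–89% at c = 0.8 and above 96% at c = 0.9.

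**The secondary figure.** A 6-month-only binary test of OR 0.75 at ICC 0.1 has about 24% power. The stated 83.4% at that ICC must therefore rest on the baseline measurements, as the protocol's description of the simulation implies.

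**The case against.** The strongest reply accepts the result at ICC 0.01 but resists anything beyond it, and most of that reply stands.

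- **A reader might infer that true power is only about 55%.** That needs an outcome confined to 0 and 7 days and a comparison that ignores baseline. The first is an inference from the 30% that appears in both paragraphs. But the two outcomes differ in source and window (RAI, past week; ODB, past month), and the Background cites 38.0% dispensed an antipsychotic. The second conflicts with the Analysis section, which models repeated measurements including baseline.
- **A reader might infer that 80% is wrong whatever the ICC.** It is not: it returns at about ICC 0.05 for a 0/7-day outcome, and at ICC 0.1 with an even spread.
- **A reader might infer that a null result would be uninformative at ICC 0.1.** The protocol's own simulation points the other way. Power of 83.4% at OR 0.75 implies a standard error of 0.288/(1.96 + 0.97) = 0.098 on the log-odds scale. OR 0.6 would then give z = 0.511/0.098 = 5.2, or above 99% power.
- **The ordering of 80% below 83.4% compares unlike methods.** One is a simulated change from baseline; the other is unexplained. The ordering is a warning sign, but the discrepancy at ICC 0.01 does not depend on it.
- **A misprint is plausible but unproven.** ICC 0.1 with an even spread gives the 80%. Equally, a 6-month-only test of OR 0.75 at ICC 0.01 gives 83–85%, close to 83.4%, so the two ICCs may have been interchanged. The document cannot decide between these.

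None of this rescues the sentence as printed. Baseline credit cannot explain it, because power already exceeds 99% without any.

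**Conclusion.** The statement of 80% power is wrong as written. With the stated clusters, cluster size, ICC 0.01 and OR 0.6, power is above 99% for every distribution of the remaining 70%, and the OR detectable with 80% power is about 0.76 to 0.81. This rests only on the protocol's inputs, equal cluster sizes and a two-sided 5% test.

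The tenfold gap between the two ICCs is unexplained. At ICC 0.1, power for OR 0.6 is about 53% to 80% on 6-month data alone, set by the unstated category distribution, and it is higher when the between-period correlation is strong. The documents do not support a single figure at ICC 0.1, a claim that the trial is underpowered, or a choice of 0.1 as the right ICC.

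**What to change.** Go back to the original calculation and establish which ICC, control-arm distribution over 0 to 7 days and method produced the 80%. Reconcile the ICCs in the two paragraphs, or explain why they differ.

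Then replace the sentence with a power figure or detectable OR that follows from a stated ICC, distribution and method, plus the between-period correlation if baseline is credited. Show both ICCs: above 99% at 0.01, and about 53% to 80% at 0.1 for 6-month data alone with the distribution specified. Rerunning the existing simulation for the primary outcome would supply the baseline-adjusted figure.

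The cost is one rewritten paragraph and one simulation rerun. The number of homes, the allocation and the analysis model are untouched.

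### The stated 80% power for the primary outcome does not follow from its own inputs: at ICC 0.01 power at OR 0.6 exceeds 99%, and the tenfold gap to the ICC of 0.1 used next is unexplained

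*Protocol*

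**What the plan says.** The Power section of the protocol makes two statements about antipsychotic use.

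- **Clusters.** The 58 homes (38 and 20) are reduced because some share prescribers: "After grouping homes sharing providers together, we anticipate a total of 45 independent clusters (30 intervention, 15 control").
- **Primary outcome** (days with an antipsychotic in the last week, 0 to 7, from RAI). The 45 "homes with 2:1 allocation will yield 80% power to detect a cumulative Odds Ratio" of 0.6, "assuming an intracluster correlation coefficient (ICC) of 0.01 and an average of 120 residents per home". With 30% of controls taken to be at 7 days, the effect is illustrated thus: "an OR of 0.6 implies a reduction in this proportion in the intervention arm to 20"%. The proportions with 0 to 6 days are not given.
- **Secondary outcome** (any antipsychotic prescription in the past month, from ODB). Power of 83.4% is claimed for an odds ratio of about 0.75 on the difference in change from baseline to 6 months. "For this simulation, we assumed a conservative ICC of 0.1, an average of 120 residents per home, and a control arm proportion of 30"%.

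The Analysis section sets the test level ("statistical significance will be assessed at the 5% level") without naming the number of sides. It plans a mixed model over the repeated time points, in which "Random intercepts and slopes will be specified to account for intracluster" and inter-period correlations.

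**The concern.** The primary power sentence prints every main input except the full day distribution, so it can be checked. With 120 residents per cluster, an ICC of 0.01 inflates the variance only about twofold, and 5,400 residents should then detect an odds ratio well short of 0.6. In the next paragraph the same drug class, number of clusters, cluster size and 30% control proportion go with an ICC ten times larger.

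The number of homes is fixed by logistics, so the use of this section is to tell a reader what effect the trial could detect. As printed, the reader cannot tell whether the primary comparison has power above 99% at 0.6 or something much lower. That affects how a null result would be read.

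**Working it through.** **Inputs from the protocol.** 15 control and 30 intervention clusters; m = 120; ICC 0.01 (primary) or 0.1 (secondary); OR 0.6; 30% of controls at 7 days; 5% level. **Assumed:** two-sided test (one-sided only raises power); day distributions as labelled.

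**Effect size.** Control odds are 0.3/0.7 = 0.4286. Multiplied by 0.6 this is 0.2571, so the intervention proportion is 0.2571/1.2571 = 20.45%. The protocol's 20% agrees after rounding.

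**Trying to reproduce the 80%.** Design effect = 1 + (m − 1) × ICC = 1 + 119 × 0.01 = 2.19. The 1,800 and 3,600 residents become 1,800/2.19 = 822 and 3,600/2.19 = 1,644.

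*Binary check (7 days or not).* SE = √(0.30 × 0.70/822 + 0.2045 × 0.7955/1,644) = 0.0188. The difference is 0.0955, so the ratio is 5.07 and power is Φ(5.07 − 1.96) = 99.9%. With a t reference on 43 df it is 99.86%.

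*Proportional-odds (Whitehead) formula.* V = n₁n₂/(3N) × (1 − Σp̄³), power = Φ(|ln OR|√V − 1.96), |ln 0.6| = 0.511. Before deflation, n₁n₂/(3N) = 1,800 × 3,600/(3 × 5,400) = 400.

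| Control distribution (30% at 7 days) | 1 − Σp̄³ | V at ICC 0.01 | Power at OR 0.6 | OR with 80% power |
|---|---|---|---|---|
| Other 70% in one category | 0.566 | 400 × 0.566/2.19 = 103 | 99.9% | 0.76 |
| 64% at 0 days, 1% at each of 1–6 | 0.650 | 119 | over 99.9% | 0.78 |
| 10% at each of 0–6 days | 0.975 | 178 | over 99.9% | 0.81 |

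A simulation of the 0–7 outcome with cluster-level t tests (4,000 runs) gave 99.95% or more. The lowest figure from any variant tried was 98.6%, with an assumed coefficient of variation of cluster size of 1.0. The 80% is not reproduced.

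**ICC that would give 80% at OR 0.6, post-intervention data only.** The required V is ((1.96 + 0.84)/0.511)² ≈ 30.1.

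- One category: design effect = 400 × 0.566/30.1 = 7.5, so ICC = 6.5/119 ≈ 0.055.
- Mostly at 0 or 7 days: ICC ≈ 0.064.
- Even spread: design effect = 400 × 0.975/30.1 ≈ 13.0, so ICC = 12.0/119 ≈ 0.10.

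**Power at ICC 0.1, post-intervention data only.** The design effect is 1 + 119 × 0.1 = 12.9, leaving about 140 and 279 effective residents.

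- Binary, t with 43 df: 53%.
- Binary or two-category, normal reference: 57–58%.
- Mostly at 0 or 7 days: about 63%.
- ICC taken on the latent logistic scale: 69–71%.
- Even spread: V = 400 × 0.975/12.9 = 30.2, so Φ(0.511 × 5.50 − 1.96) ≈ 80%.

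**Power at ICC 0.1 if baseline is used.** For a difference in change in proportions, with different residents at each time, the variance per cluster is 2 × 0.1 × 0.21 × (1 − r) + 0.9 × [p₀(1 − p₀) + p₆(1 − p₆)]/120. Here r is the correlation of a home's rate between periods, which the protocol does not give.

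| r (assumed) | 1.0 | 0.95 | 0.9 | 0.8 |
|---|---|---|---|---|
| Power at OR 0.6 | over 99.9% | 98.8% | 94.4% | 80.6% |

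Other versions of this calculation gave 78% to 89% at r = 0.8, and one gave 65% at r = 0.7.

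**Two sensitivity points.** If 58 homes average 120 residents, 45 clusters average 58 × 120/45 = 155, and they are unequal. With 155 per cluster, equal sizes and ICC 0.01, power at OR 0.6 is still over 99.9%. For the secondary 83.4% (OR 0.75, ICC 0.1), post-intervention data alone give about 24%, so the figure needs the gain from baseline. Simulation of the difference in change gives about 82–83% at r = 1.0, 59% at 0.9 and 44% at 0.8, if residents at the two times are independent.

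**The case against.** Four points can be made for the protocol.

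1. **At the printed ICC the error is in the safe direction.** Power is understated. This stands, but a power figure that its inputs do not deliver is still wrong, and the 80% and the 0.01 cannot both be relied on.
2. **The two ICCs belong to different outcomes.** One is a weekly count of days from RAI, the other any prescription in a month from ODB, and the protocol calls 0.1 conservative. This stands in part. It shows that a gap is possible, but gives no reason for a tenfold one, and ICC 0.01 would still not give 80%.
3. **A reader might infer that the trial is underpowered.** The documents do not support that. The 53–80% range ignores baseline, whereas the planned model uses baseline, 3-month and 6-month data and adjusts for the stratification factors, which include baseline antipsychotic rates. Nothing in the protocol shows that 0.1 is the right ICC for the primary outcome.
4. **A reader might infer that the cluster size of 120 and the 83.4% are also errors.** That is not shown. Leaving out the extra residents in merged clusters understates the sample, and any loss from unequal sizes needs a coefficient of variation that the protocol does not give. The 83.4% does not require perfectly stable home rates: with an assumed within-resident correlation of 0.5 or 0.7, it is reached at r of about 0.95 or 0.94. Both are undisclosed assumptions.

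**Conclusion.** The primary power statement is wrong as written. With 45 clusters at 2:1, 120 residents and ICC 0.01, power at a cumulative odds ratio of 0.6 is over 99%, and 80% power belongs to an odds ratio of about 0.76 to 0.81. This does not depend on the unstated distribution of days, and using baseline would not bring power at ICC 0.01 down to 80%.

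The printed 80% at 0.6 fits a post-intervention comparison with an ICC of about 0.05 to 0.10, and an even spread over 0 to 6 days gives 80% almost exactly at 0.1. That is consistent with 0.01 being a slip for 0.1, but the document cannot prove it.

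If 0.1 is the right value, power at 0.6 is about 53% to 80% without baseline, and about 80% to over 99% with it for assumed between-period correlations of 0.8 to 1.0. A shortfall in power is therefore possible but not established.

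**What to change.** In the Power section of the protocol:

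- Correct the primary ICC if 0.01 is a slip, or justify it against the 0.1 used for the dichotomous antipsychotic outcome.
- Restate the primary power and the detectable odds ratio so that ICC, power and odds ratio agree. Give the calculation method, the assumed control distribution over 0 to 7 days, and whether baseline is used and with what between-period correlation.
- Show results over ICC 0.01 to 0.1.
- As sensitivity checks, show the effect of unequal merged clusters (58 homes in 45 clusters), and state the between-period correlation behind the 83.4%.

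The cost is one rerun and a reworded section. No homes, procedures or analyses change.

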### **Recruitment**

The recruitment process of LTC homes is described below.

In summary, recruitment of LTC homes will occur by emails co-signed by the OMA, MOHLTC, and local LHIN leads to eligible LTC home administrative leads and from other stakeholders (i.e., local physician leads) to medical directors of eligible LTC homes, with follow up phone calls as required. Some LTC homes have already expressed interest as they heard about the project being developed. These will be contacted again to confirm willingness to be involved in the interventions and the evaluation. Messaging during recruitment will focus on a few key concepts to mitigate concerns: 1) there is no downside, since randomization to not receive the outreach means continuing to function as usual with no added mandatory burdens or costs; 2) randomization will be skewed so that chances of receiving the intervention are greater than 50%; 3) we wish to observe what would happen in real-life, so consenting to the trial does not commit them to do anything they feel is not their residents' best interest; 4) evaluations will be conducted at the aggregate level to protect confidentiality.

To date, the project team have developed a plan that has identified >30 potential LTC homes in each region of the province where the project will occur. Recruitment will attempt to preferentially focus on LTC homes known to have higher antipsychotic rates. Identification of additional homes will be done in collaboration with the LHINs and other stakeholders and will be focused on first recruiting those homes with highest baselines antipsychotic prescribing rates and the lowest prescriber overlap. If greater than 58 homes are recruited, then the excess homes allocated will receive 'audit and feedback only' as the educational outreach will be limited to 38 homes total.

No recruitment of patients is required or planned.

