### **Allocation**

Participating LTC homes will be allocated to one of the two arms of the study (active/full intervention versus standard education) using a 2:1 allocation ratio, after stratifying on hub, baseline antipsychotic prescription rates (using published CIHI reports), and size (number of eligible patients). A 2:1 allocation ratio will be used to satisfy the requirements of the sponsor and to improve feasibility of recruitment of homes. LTC homes that share prescribers will be allocated as a unit to avoid contamination. Due to funding restrictions, no more than 38 homes will be allocated to the intensive intervention; if more than 60 homes are recruited, the allocation ratio will be less than 2:1, but the odds of allocation to the full intervention will remain greater than 1:1. Allocation will be conducted by an independent statistician using computer-generated random numbers.

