| 20 homes
PHASE 1             |                                 | Allocated to
EO (Topic 1) |                                 | Qualitative
process
evaluation | 6M follow
up
complete     |                                 | 6M ICES
ODB data
complete |                          |                                      |                                 |                                                           |
| 20 + homes
PHASE 1           |                                 | Allocated to
AF only      |                                 | Qualitative
process
evaluation | 6M follow
up
complete     |                                 | 6M ICES
ODB data
complete |                          |                                      |                                 | Potential
launch of
EO (if
scale-up
approved) |
| 20 homes
PHASE 2             |                                 |                              |                                 |                                      | Allocated
to EO
(Topic 1) |                                 |                                 | 6M follow
up complete |                                      | 6M ICES
ODB data
complete |                                                           |
| Topic 2 (Falls)                 |                                 |                              |                                 |                                      |                                 |                                 |                                 |                          |                                      |                                 |                                                           |
| All
Intervention
Homes
(n=40) |                                 |                              |                                 |                                      |                                 | Introduction of
EO Topic 2   |                                 |                          | Qualitative
process
evaluation |                                 |                                                           |

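### The rule for homes beyond the 58th can be read as non-random assignment to control, and it conflicts with the Allocation section on both rule and threshold

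*Protocol*

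**What the plan says.** Two sections of the protocol say what happens when more homes join than planned.

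- **Allocation.** Participating homes are allocated 2:1 after stratification on hub, baseline antipsychotic rate and size, and homes that share prescribers move as a unit. The mechanism is explicit: "Allocation will be conducted by an independent statistician using computer-generated random numbers". There is a ceiling: "no more than 38 homes will be allocated to the intensive intervention". For larger numbers, "if more than 60 homes are recruited, the allocation ratio will be less than 2:1". A floor is set as well: "the odds of allocation to the full intervention will remain greater than 1:1".
- **Recruitment.** "If greater than 58 homes are recruited, then the excess homes allocated will receive" audit and feedback only, and the reason given is the ceiling: "as the educational outreach will be limited to 38 homes total". The same section tells homes that their chance of outreach is above 50%. It also sets the order of approach for additional homes: "first recruiting those homes with highest baselines antipsychotic prescribing rates and the lowest prescriber overlap".

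The Power section plans 58 homes, at most 38 with outreach and 20 with usual care, and expects 45 independent clusters (30 and 15) once homes sharing providers are grouped. The roll-out table under Implementation leaves the number of audit-and-feedback homes open at 20 or more, and shows 40 intervention homes.

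**The concern.** Taken at its word, the Recruitment sentence gives home 59 and later homes a zero probability of outreach. The Allocation section gives the same homes better than even odds. Both cannot be followed, and the subject is the assignment mechanism of a randomised trial. The literal rule also contradicts the Recruitment section's own message about a chance above 50%.

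The identity of the extra homes matters. If high-prescribing homes are sought first, homes that join late will probably prescribe less. Placing all of them in control would tie the arm to the baseline level of the primary outcome, and no chance mechanism would stand behind their assignment.

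Recruiting more than 58 homes is not far-fetched. The Recruitment section reports more than 30 potential homes in each region, and the Eligibility section speaks of regions in the plural, so the pool exceeds 60.

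**Working it through.** **Inputs.** Cap of 38 outreach homes (Allocation, Recruitment). Planned split 38 + 20 (Power). Ratio 2:1, threshold 60 and lower bound 1:1 (Allocation). Threshold 58 (Recruitment).

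**The plan's own figure.** 38 + 20 = 58 homes, as stated. The ratio is 38/20 = 1.9:1.

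**Where the cap binds.** An exact 2:1 split of N homes needs 2N/3 outreach places. Setting 2N/3 = 38 gives N = 38 × 3/2 = 57, so the ratio must fall below 2:1 from the 58th home. At 60 homes, 2:1 would need 40 outreach places, two above the cap. The figure of 60 would fit the 40 intervention homes in the roll-out table, but it does not fit 38.

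**If all N homes are randomised to 38 outreach places.** The chance of outreach is 38/N and the odds are 38/(N − 38).

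**If the Recruitment sentence is followed literally.** The first 58 homes have chance 38/58 = 0.655 and each later home has chance 0. The non-randomised share of the control arm is (N − 58)/(N − 38).

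| Homes N | Chance if all randomised | Odds | Non-randomised share of controls, literal rule |
|---|---|---|---|
| 58 | 0.655 | 1.90 | 0 |
| 60 | 0.633 | 1.73 | 2/22 = 9% |
| 65 | 0.585 | 1.41 | 7/27 = 26% |
| 70 | 0.543 | 1.19 | 12/32 = 38% |
| 75 | 0.507 | 1.03 | 17/37 = 46% |
| 76 | 0.500 | 1.00 | 18/38 = 47% |

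The promise of odds above 1:1 therefore holds up to 75 homes and fails at 76.

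These are counts of homes, as are the cap and both thresholds. Randomisation is by prescriber-sharing unit, so the achieved numbers may differ by the size of a unit. In expected units the plan is exactly 2:1 (30 and 15).

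**Illustration of baseline imbalance (assumed rates).** The protocol gives no rates for early and late homes. Take 30% for the first 58 homes, which borrows the control proportion in the Power section, and assume 25% to 27% for later homes. Control baseline = (20 × 30 + e × late)/(20 + e), with e = N − 58.

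- N = 65, e = 7: (600 + 175)/27 = 28.7% to (600 + 189)/27 = 29.2%, which is 0.8 to 1.3 points below the outreach arm.
- N = 75, e = 17: (600 + 425)/37 = 27.7% to (600 + 459)/37 = 28.6%, which is 1.4 to 2.3 points below.

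A wider assumed gap (early homes 32% to 34%, late homes 22% to 25%) gives 1.2 to 2.0 points with four extra homes and 2.0 to 3.4 with eight. If all homes are randomised, the expected difference is zero.

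**The case against.** A reader might infer that the protocol assigns late homes to control by order of recruitment, and that this breaks the randomised comparison and the intention-to-treat claim. The text does not support that.

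- **No order rule is written.** The Recruitment sentence does not say how the excess homes are identified or that they skip randomisation. It can be read as saying that extra places are control places: all homes are randomised, 38 get outreach, and the rest are controls. Apart from the threshold, that agrees with the Allocation section, which is the section that governs assignment. The instruction to approach high-rate homes first concerns recruitment, not assignment.
- **The open control count is neutral.** A fixed outreach cap with a falling random ratio would also produce 20 or more control homes. The roll-out table marks consent before the first allocation, which suits allocation from an assembled list.
- **Prescriber-sharing homes.** Nothing in the Recruitment section overrides the rule that they are allocated as a unit, so splitting them is speculation.
- **Existing protection.** Baseline rate is a stratification factor, the prescribing analysis adjusts for the stratification factors, and the model has an intervention-by-time term. A raw baseline difference is therefore not the bias in the planned estimate.
- **Yardstick.** The drop from 30% to about 25% in the Power section belongs to the dichotomous secondary outcome. The primary outcome's target is 30% to 20%, so imbalances of one to three points should be judged against ten points, not five.

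All of this stands, and it limits the point to an ambiguity with a conditional consequence. It does not remove the point. If every home is randomised, no identifiable homes are in excess, so the sentence more naturally describes homes after the 58th. Adjustment would reduce an imbalance but would not make those homes randomised. The thresholds also disagree under either reading.

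**Conclusion.** The point holds as an inconsistency that needs correcting. The two sections give different thresholds (58 and 60), and the Recruitment sentence, read literally, gives a different rule. The threshold of 60 is also inconsistent with the cap of 38, and the 1:1 floor has an unstated limit of 75 homes. These statements need only the protocol's own figures.

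Harm to the comparison requires three things together: more than 58 homes recruited, the literal reading followed, and the extra homes analysed as controls. The protocol establishes none of them. The Power section includes 58 homes in the trial, and no section says whether excess homes would enter the analysis. If all three held, the non-randomised share of controls would run from 9% at 60 homes to 46% at 75. The resulting imbalance cannot be derived from the protocol; the figures of about one to three points rest on assumed rates and ignore the planned adjustment. At 58 homes or fewer there is no effect.

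**What to change.** Replace the Recruitment sentence with a single rule, and use it in both sections. All recruited homes, grouped into prescriber-sharing units, are randomised, with outreach capped at 38 homes and the ratio set before allocation. State that the ratio falls below 2:1 once more than 57 homes are recruited, and that the promise of odds above 1:1 is valid up to 75 homes. Bring the 40 intervention homes in the roll-out table into line with the cap.

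The roll-out table schedules both allocations before the date of this version (30 May 2016), so an analysis rule is needed as well. Any home given audit and feedback without random allocation is left out of the primary comparison and shown only in a sensitivity analysis. The table has the phase 1 six-month dispensing data complete only in July-August 2016, so on that schedule the rule could be fixed before those results.

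The cost is a few sentences and, at worst, the loss of a few control homes from the primary analysis.
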